**8.5 Serious adverse events**

(1) Definition of SAEs

SAEs refer to medical events that occur during a clinical study that require hospitalization or prolonged hospitalization, result in disability, affect participants’ ability to work, are life-threatening or fatal, or lead to congenital malformations. Major unexpected medical events include the following:

⚫ Events leading to death;

⚫ Life-threatening events (defined as risk of death at the time of onset);

⚫ Events that require hospitalization or prolonged hospitalization;

⚫ Events that can lead to permanent or severe disability/dysfunction; and

⚫ Congenital abnormalities or birth defects.

(2) Pregnancy

Pregnancy that occurs during the clinical study will be reported as an SAE.

(3) Disease progression

Disease progression (including progressive signs and symptoms) will not be reported as an SAE. However, death due to disease progression during the study or safety reporting period will be reported as an SAE. Hospitalization due to progressive signs and symptoms will not be reported as an SAE. If cancer patients die during the study or safety reporting period, the event leading to death will be reported as an SAE.

(4) Other anticancer treatments

If the subject starts to receive other anticancer treatments, non-fatal AEs will be reported as of the start of new anticancer treatments. If death occurs during the SAE reporting period after the end of study treatment, SAEs will be reported regardless of whether the patient receives other treatments.

(5) Hospitalization

All AEs that result in hospitalization or prolonged hospitalization during the clinical study will be considered SAEs. Any initial admission (even if it is less than 24 hours) will be considered hospitalization.

Hospitalization does not include the following:

⚫ Rehabilitation facilities or nursing homes;

⚫ Regular emergency room admission; and

⚫ Same-day surgery (such as outpatient/same-day/ambulatory surgery).

Hospitalization or prolonged hospitalization unrelated to worsening AEs will not be considered SAEs:

⚫ Admission due to a preexisting condition, without any new AE or worsening of the preexisting condition (such as to check preexisting, ongoing laboratory abnormalities before the study);

⚫ Hospitalization due to administration or insurance (such as annual routine check-up);

⚫ Hospitalization specified in the study protocol (such as procedures specified in the protocol);

⚫ Elective hospitalization unrelated to worsening of an AE (such as elective cosmetic surgery);

⚫ Scheduled treatment or surgery will be recorded in the protocol and/or the subject’s baseline data; and

⚫ Admission to receive blood products.

Diagnostic or therapeutic invasive (such as surgery) and noninvasive procedures will not be reported as AEs. However, any condition that results in a procedure will be reported if it meets the criteria for AEs. For example, acute appendicitis that occurs during the AE reporting period will be reported as an AE, but appendectomy will be recorded as the treatment of this AE.

(6) SAE reporting procedures

The SAE reporting period will be from signing the ICF through 30 calendar days after the last dose of apatinib mesylate tablets (including the 30^th^ day). During the study, any SAE will be reported to the clinical monitor and PIs within 24 hours and reported on the New Drug Clinical Study Serious Adverse Event (SAE) Reporting Form (signed and dated), which will be promptly faxed to the sponsor, lead site(s), Ethics Committee of clinical sites, NMPA, and the investigator’s regional (provincial or metropolitan) FDA.

During continued treatment after the end of the study, any SAE will be reported to the sponsor within 24 hours. All SAEs will be recorded on an SAE reporting form. All SAEs that occur from the start of continued treatment through 30 days after the last dose will be reported. SAES that occur after the 30-day period will not generally be reported unless they are suspected to be related to apatinib mesylate tablets.

For SAEs, the symptoms, severity, time of onset, time of treatment, measures taken, follow-up time and method, and outcomes will be carefully monitored and recorded. If the investigator believes that an SAE is unrelated to apatinib mesylate tablets but is potentially related to the study conditions (such as discontinuation of previous treatment or comorbidities during the study), the relationship will be explained in an SAE narrative on a CRF. If the intensity of an ongoing SAE or its relationship to apatinib mesylate tablets changes, a follow-up SAE report will promptly sent to the sponsor. All SAEs will followed up until resolution or stabilization.

Note: SAE contacts

| Institution | Contact | Phone | Fax |
| --- | --- | --- | --- |
| NMPA | Safety Monitoring Committee | [name] | [name] |

**9. Statistical Processing**

**9.1 Analysis populations**

Safety set (SS): safety data set that will include all enrolled subjects who have received at least one dose of apatinib mesylate tablets and have at least one safety evaluation;

FAS: an intent-to-treat (ITT) data set that will include all randomized subjects who have received at least one dose of the apatinib mesylate tablets; subjects who did not receive any treatment after randomization and who do not meet inclusion criterion 2 will be excluded from FAS; and

Per-protocol set: a subset of FAS that will include all per-protocol, compliant subjects who did not receive any other GC treatment during the study and who have complete CFR data. Missing data will not be imputed.

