**Synopsis**

| Study Title | | A prospective, open-label, single-arm, multicenter, phase IV clinical study of apatinib mesylate tablets for the treatment of advanced gastric cancer or gastroesophageal junction adenocarcinoma following second-line chemotherapy failure in China |
| --- | --- | --- |
| Protocol Number | | AHEAD |
| Version Number/Date | | 2.2/12-21-2015 |
| Sponsor(s) | | Hengrui Pharmaceuticals Co., Ltd. |
| Nature | | Postmarketing phase IV clinical study of a new drug in accordance with the requirements for approval by the National Medical Products Administration |
| Subjects | | Patients with advanced gastric cancer or gastroesophageal junction adenocarcinoma following at two lines chemotherapy failure |
| Study  Objectives | Primary Objective | To evaluate the safety of apatinib mesylate tablets in patients with advanced gastric cancer or gastroesophageal junction adenocarcinoma following at least two lines chemotherapy failure |
|  | Secondary Objective | To evaluate the effectiveness of apatinib mesylate tablets in patients with advanced gastric cancer or gastroesophageal junction adenocarcinoma following second-line chemotherapy failure |
| Study Design | | Prospective, open-label, single-arm, multicenter phase IV clinical study in China |
| Planned Enrollment | | 2000 patients |
| Number of Sites | | 100 |
| Principal Investigator(s) | | [name]; [name] |
| Lead Site(s) | | Fudan University Shanghai Cancer Center; PLA 81 Hospital |

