**3. Study Design and Protocol**

**3.1 Description of study design**

This is a multicenter, prospective, open-label, single-arm, phase Ⅳ clinical study in China that is designed to evaluate the safety and effectiveness of apatinib mesylate tablets for the treatment of AGC or gastroesophageal junction adenocarcinoma following second-line chemotherapy failure. Therefore, the data collected and reported will comprehensively reflect the real-world data of apatinib mesylate tablets for the treatment of AGC or gastroesophageal junction adenocarcinoma following second-line chemotherapy failure.

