**4.2 Inclusion and exclusion criteria**

**4.2.1 Inclusion criteria**

1. Age: 18 to 75 years old, men or women;

2. Pathologically and/or cytologically confirmed advanced gastric or gastroesophageal junction adenocarcinoma, with an extragastric measurable lesion (spiral computed tomography (CT) ≥ 10 mm, conforming to RECIST 1.1);

Note: Patients without any gastric or extragastric measurable lesion but with an observable lesion can be enrolled after a comprehensive evaluation by investigators from each institution to observe QoL and survival. These patients will be excluded from the evaluation of objective response.

3. Patients with AGC or gastroesophageal junction adenocarcinoma following ≥ second-line chemotherapy failure;

Note: (1) Definition of treatment failure: disease progression during treatment or tumor relapse and metastasis after treatment or intolerable toxicity; (2) for PD, each line of treatment is ≥ 1 cycle or longer with one or more chemotherapy drugs; pilot adjuvant/neoadjuvant therapy is allowed and will be considered first-line systemic chemotherapy for PD in the case of tumor relapse and metastasis during treatment or within 24 weeks after treatment; and (3) upfront therapy can be chemotherapy combined with molecular targeted drugs.

4. Eastern Cooperative Oncology Group (ECOG) performance status (PS) score: 0-2;

5. Normal vital organ functions based on the following standards:

(1) Complete blood count (CBC) (no blood transfusion within 14 days):

a. Hemoglobin (Hb) ≥ 90g/L;

b. Absolute neutrophil count (ANC) ≥ 1.5 × 10^9^/L; and

c. Platelet (PLT) count ≥ 80 × 10^9^/L.

(2) Serum biochemistry:

a. Bilirubin (BIL) < 1.5× upper limit of normal (ULN);

b. Alanine aminotransferase (ALT) and aspartate aminotransferase (AST) < 2.5× ULN; or < 5× ULN in the case of liver metastasis;

c. Serum creatinine (Cr) ≤ 1× ULN, endogenous creatinine clearance ≥ 50 ml/min (Cockcroft-Gault formula);

6. Expected survival ≥ 3 months;

7. The treating physician planned to use apatinib mesylate tablets for treatment;

8. Voluntary participation, with a signed informed consent form (ICF); and

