**9.4 Determination of sample size**

Number of subjects: n = 2000

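### The FAS is built on a randomization that this single-arm study does not have, and its criterion 2 exclusion can be read as removing patients enrolled to observe survival and QoL

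*Protocol*

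**What the plan says.** The Synopsis and section 3.1 both describe a study with one arm: "This is a multicenter, prospective, open-label, single-arm". No section describes a random allocation.

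Section 9.1 nevertheless defines the FAS as "an intent-to-treat (ITT) data set that will include all randomized subjects who have received at least one dose of the apatinib mesylate tablets". It then adds an exclusion: "subjects who did not receive any treatment after randomization and who do not meet inclusion criterion 2 will be excluded from FAS". The per-protocol set is a subset of the FAS. The safety set, defined in the same section, is based on enrolled subjects who were dosed and had a safety evaluation. It mentions neither randomization nor criterion 2.

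The main sentence of inclusion criterion 2 (section 4.2.1, repeated in the Synopsis) has two parts. One is the diagnosis: "Pathologically and/or cytologically confirmed advanced gastric or gastroesophageal junction adenocarcinoma". The other is a measurable lesion outside the stomach. A Note placed under the same criterion makes an exception for patients who have an observable lesion but no measurable one. They "can be enrolled after a comprehensive evaluation by investigators from each institution to observe QoL and survival", and the Note keeps them out of the objective response evaluation. It states no other restriction.

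Section 9.3.3 gives the methods for OS, PFS, ORR and DCR without naming an analysis set for any of them.

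**The concern.** Two things look wrong. First, membership of the FAS depends on an event that never occurs in this study. Second, the exclusion points to the criterion that contains the measurable-lesion requirement, while the Note to that criterion deliberately admits patients without such a lesion so that their survival and QoL can be followed. A general analysis set that dropped them would contradict the reason for enrolling them.

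What is at stake is who enters the effectiveness estimates. Two analysts working from the same data and the same section 9.1 could build different populations for OS, PFS and QoL. Section 1.2 says the study is meant to close the gap left by premarketing studies with many exclusion criteria, and dropping dosed patients at the analysis stage would work against that. Section 9.3.1 has the statistical analysis plan developed from the protocol, so the conflict would pass into it unless it is resolved.

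**Working it through.** No calculation underlies this point. The check is to apply section 9.1 to each kind of subject.

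**Step 1: the randomization condition.** The FAS requires a subject to be randomized and dosed. In a single-arm study the number randomized is 0, so the FAS has 0 members, and so does the per-protocol set drawn from it. The safety set refers to enrolled subjects and can be built as written.

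**Step 2: what the exclusion sentence adds.** Replace *randomized* by *enrolled*, as the safety set does, and apply the rest. The two conditions (untreated; criterion 2 not met) are joined by *and*, which can mean that both must hold or that each is a separate ground for exclusion.

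| Subject | In FAS by the dose rule? | Excluded if both must hold? | Excluded if either suffices? |
|---|---|---|---|
| Untreated, meets criterion 2 | No | already out | already out |
| Untreated, fails criterion 2 | No | already out | already out |
| Dosed, meets criterion 2 | Yes | No | No |
| Dosed, fails criterion 2 | Yes | No | **Yes** |

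If both conditions must hold, the sentence changes nothing, because the dose rule has already removed every untreated subject. The criterion 2 phrase has an effect only on the either/or reading, and that effect is to remove dosed subjects.

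**Step 3: who fails criterion 2, on the either/or reading.**

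| Dosed subject | Criterion 2 = main sentence only | Criterion 2 = main sentence plus Note |
|---|---|---|
| Diagnosis not confirmed | Removed | Removed |
| Confirmed, observable but no measurable lesion, enrolled under the Note | **Removed** | Kept |
| Confirmed, extragastric measurable lesion | Kept | Kept |

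The conflict with the Note is confined to one cell: either/or, with criterion 2 taken as its main sentence.

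**Step 4: which endpoints follow.** Section 9.3.3 names no set. Section 9.1 offers three: one for safety, the FAS with its intent-to-treat label, and a subset of the FAS. The protocol's account of the phase III trial (section 1.1.3.3) reports median OS on the FAS and on the per-protocol set. The FAS is therefore the natural effectiveness set here, by inference. If it is, subjects removed in step 3 are lost from OS, PFS and QoL.

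**Step 5: size.** The planned number is 2000 (section 9.4). If a share p of dosed patients has no measurable lesion, 2000 × p are affected, that is 2000 × 0.01 = 20 per percentage point if all are dosed. The protocol does not give p.

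**The case against.** The strongest reply is that the protocol can be read without any contradiction. The Note sits inside criterion 2, so a patient admitted under it can fairly be said to meet the criterion and stays in the FAS. Criterion 2 also covers confirmation of the diagnosis, so the exclusion may be meant only for subjects without the target disease, which does not conflict with the Note. Read strictly, *and* removes no treated subject at all. Assigning endpoints to analysis sets can properly be left to the statistical analysis plan. The safety set shows what the FAS wording was meant to say, and only secondary, descriptive estimates are involved.

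Much of this stands. A reader might infer that the protocol definitely removes all patients without measurable disease from OS, PFS and QoL. The text does not support that: it takes the either/or reading, a criterion 2 without its Note, and the FAS as the effectiveness set. Nor does the protocol say that these patients differ systematically from the others, so a direction of bias in the survival estimates cannot be claimed.

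The objection does not make the section sound. The strict reading of *and* leaves the exclusion without any function. Nothing in section 9.1 says that meeting criterion 2 includes entry under the Note, or that only the diagnosis is meant. The reference to randomization is a wrong statement, not a detail left for later.

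**Conclusion.** Section 9.1 is wrong as written and should be fixed. The randomization part is certain: taken literally, neither the FAS nor the per-protocol set has any members, although the intended wording is easy to guess from the safety set.

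The criterion 2 part is conditional. On the only reading that gives the exclusion an effect, and if criterion 2 means its main sentence alone, it removes dosed patients whom the Note enrols for survival and QoL and bars only from objective response. Their loss from OS, PFS and QoL further assumes that the FAS is used for those endpoints.

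The size cannot be established from the protocol. Purely as an illustration, an assumed share of 10% to 25% would be 0.10 × 2000 = 200 to 0.25 × 2000 = 500 patients, but nothing in the document supports that range. The primary endpoint is safety, and the safety set carries neither defect, so the main conclusion of the study is not at risk.

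**What to change.** Rewrite the FAS definition in section 9.1:

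- FAS: all enrolled subjects who received at least one dose of apatinib, to be used for OS, PFS and QoL. Delete both references to randomization.
- If an exclusion tied to criterion 2 is kept, limit it to subjects whose disease lacks pathological and/or cytological confirmation. Deleting it outright would also discard that condition.
- State that patients enrolled under the Note to criterion 2 stay in the FAS.
- Add a response-evaluable set for ORR: FAS subjects with a baseline measurable lesion as criterion 2 requires, which includes its being extragastric.
- State whether DCR uses the response-evaluable set or the FAS. The Note mentions only objective response, so it does not settle this.

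The cost is a wording amendment, carried into the statistical analysis plan before database lock. No new data are needed: dosing, the diagnosis and baseline imaging are already part of the planned records.

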**9.2 Analysis variables**

**9.2.1 Primary measures**

AEs will be coded according to MedDRA, and each AE will be assigned a system organ classification (SOC) and a preferred term. The severity of AEs will be evaluated in accordance with NCI CTCAE 4.0.

The primary endpoints will include the incidence and severity of AEs.

**9.2.2 Secondary measures**

**a. Safety measures**

⚫ The incidence of treatment-emergent AEs

⚫ The incidence of AEs leading to treatment discontinuation and/or early withdrawal

⚫ The incidence of SAEs and drug-related SAEs

⚫ Mortality

⚫ Drug discontinuation due to AEs

⚫ Changes in vital signs after treatment (heart rate, blood pressure, temperature, respiration)

⚫ Changes in physical examination results after treatment

⚫ Clinical laboratory abnormalities

**b. Efficacy measures:**

⚫ OS, defined as the time from study entry (signing the ICF) to all-cause death. For subjects who are alive at the last follow-up, the last follow-up date is censored for OS.

⚫ PFS, defined as the time from study entry (signing the ICF) to tumor progression or all-cause death. For subjects without tumor progression or death, the last valid tumor evaluation date is censored for PFS.

⚫ ORR: CR + PR

⚫ DCR: CR + PR + SD

Note: The RECIST criteria are used mainly for the observation and evaluation of objective responses to cytotoxic chemotherapy drugs and cannot comprehensively or accurately reflect the efficacy of molecular targeted drugs. Apatinib mesylate tablets may be continued, under close monitoring, if medical imaging indicates significant degeneration, necrosis, or liquefaction in the lesion even though the lesion has grown or if clinical symptoms and/or QoL improve, the treating physician believes that treatment continuation will bring survival benefits, and the patient has no significant adverse reactions and is willing to continue treatment.

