**Study Schedule**

| **Item** | **Within 2 weeks before treatment** | **Within 1 week before treatment** | **Treatment Cycle** | | | | | | | | | | | |
| --- | --- | --- | --- | --- | --- | --- | --- | --- | --- | --- | --- | --- | --- | --- |
|  |  |  | **Cycle 1** | | | | **Cycle 2** | **Cycle 3** | **Cycle 4** | | | | **Cycle 5** | **Cycle 6+** |
|  |  |  | 1 w | 2 w | 3 w | 4 w |  |  | 1 w | 2 w | 3 w | 4 w |  |  |
| Signed informed consent form | **Ⅹ** |  |  |  |  |  |  |  |  |  |  |  |  |  |
| History of previous treatments |  | **Ⅹ** |  |  |  |  |  |  |  |  |  |  |  |  |
| Vital signs |  | **Ⅹ** |  |  |  | **Ⅹ** | * | * |  |  |  | **Ⅹ** | # | # |
| Physical examination |  | **Ⅹ** |  |  |  | **Ⅹ** | * | * |  |  |  | **Ⅹ** | # | # |
| Chest X-ray |  | **Ⅹ f** |  |  |  |  |  |  |  |  |  |  |  |  |
| Blood pressure **a** |  | **Ⅹ** | **3** | **3** | **2** | **2** | * | * | **1** | **1** | **1** | **1** | # | # |
| Echocardiography |  | **Ⅹ** |  |  |  | **Ⅹ b** | * | * |  |  |  | **Ⅹ b** | # | # |
| Coagulation |  | **Ⅹ** |  |  |  | **Ⅹ** | * | * |  |  |  | **Ⅹ** | # | # |
| Electrocardiogram (ECG) | **Ⅹ** |  |  |  |  | **Ⅹ** | * | * |  |  |  | **Ⅹ** | # | # |
| ECOG PS score |  | **Ⅹ** |  |  |  | **Ⅹ** | * | * |  |  |  | **Ⅹ** | # | # |
| Complete blood count |  | **Ⅹ** |  | **Ⅹ** |  | **Ⅹ** | * | * |  |  |  | **Ⅹ** | # | # |
| Urinalysis |  | **Ⅹ** |  | **Ⅹ** |  | **Ⅹ** | * | * |  |  |  | **Ⅹ** | # | # |
| Stool test |  | **Ⅹ** |  | **Ⅹ** |  | **Ⅹ** | * | * |  |  |  | **Ⅹ** | # | # |
| Liver and kidney function, electrolytes |  | **Ⅹ** |  |  |  | **Ⅹ** | * | * |  |  |  | **Ⅹ** | # | # |
| Tumor marker (CEA) |  | **Ⅹ** |  |  |  |  | **Ⅹ** | **Ⅹ** |  |  |  |  | **Ⅹ** | **&** |
| Imaging  (X-ray/CT/MRI/ultrasound B) | **Ⅹ c** |  |  |  |  |  | **Ⅹ** | **Ⅹ d** |  |  |  |  | **Ⅹ** | **&** |
| Gastroscopy |  | **Ⅹ e** |  |  |  |  |  |  |  |  |  |  |  |  |
| Quality of life score |  | **Ⅹ** |  |  |  |  | **Ⅹ** | **Ⅹ** |  |  |  |  | **Ⅹ** | **&** |
| Adverse events |  |  | **Ⅹ** | **Ⅹ** | **Ⅹ** | **Ⅹ** | * | * | * | * | * | * | * | * |
| Concomitant medications |  |  | **Ⅹ** | **Ⅹ** | **Ⅹ** | **Ⅹ** | * | * | * | * | * | * | * | * |

Note: **All measures and exams/tests, including imaging studies, should be performed according to the study schedule for each cycle and will not be affected by drug withdrawal.**

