**6.2 Screening visit**

The screening visit should be completed within 14 days before treatment cycle 1 and will include electrocardiography (ECG) and chest and abdomen CT or magnetic resonance imaging (MRI). Within 7 days before treatment, a medical history will be obtained, and tests, including ECOG PS score, physical examination, vital signs, CBC, urinalysis, stool test, gastroscopy (as needed), echocardiogram, liver and kidney function, blood electrolytes, coagulation, tumor marker (carcinoembryonic antigen (CEA)), pregnancy test (as needed), and QoL assessment, will be conducted.

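### OS and PFS are timed from consent, but every analysis set requires a first dose up to 14 days later, so both medians are lengthened by about the typical consent-to-dose lag

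*Protocol*

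**What the plan says.** Both time-to-event endpoints start at consent. Protocol section 9.2.2 b has "OS, defined as the time from study entry (signing the ICF) to all-cause death" and "PFS, defined as the time from study entry (signing the ICF) to tumor progression or all-cause death".

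Entry to every analysis set in section 9.1 depends on dosing:

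- The safety set is "all enrolled subjects who have received at least one dose of apatinib mesylate tablets and have at least one safety evaluation".
- The FAS is "all randomized subjects who have received at least one dose of the apatinib mesylate tablets", with the further rule that "subjects who did not receive any treatment after randomization and who do not meet inclusion criterion 2 will be excluded from FAS".
- The third set is described as "Per-protocol set: a subset of FAS", so it too holds dosed patients only.

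Section 9.3.3 plans Kaplan-Meier curves and medians with 95% confidence intervals. It does not name the set to be used, but no defined set contains an undosed patient.

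The Study Schedule ticks the ICF in the column headed "Within 2 weeks before treatment". Section 6.2 adds that "The screening visit should be completed within 14 days before treatment cycle 1". The lag from consent to first dose can therefore be anything from 0 to 14 days. After baseline imaging, the next scheduled tumour evaluation is at the end of cycle 2 (section 6.3).

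**The concern.** The clock starts at one event (consent) and patients qualify for analysis at a later one (first dose). The time between is credited to OS and PFS, although a patient who dies in it never enters the analysis. This is guarantee-time, or immortal-time, bias. The tumour evaluation calendar adds to it: cycles run from treatment start, so a progression found at the first on-treatment scan carries the lag on top of the two cycles.

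The trial has a single arm, so no concurrent control shares the shift and cancels it. The amount would depend on how quickly sites move from consent to dosing, not on the drug. Effectiveness is the stated secondary purpose (section 2.2), and the regulator asked for efficacy as well as safety data (section 1.2), so the medians will be read. Section 9.3.1 says the statistical analysis plan will be built on the protocol, so it would start from these definitions.

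**Working it through.** **Inputs**

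- Time origin: ICF signing (section 9.2.2 b).
- Entry condition: at least one dose (section 9.1).
- Lag L from consent to first dose: at most 14 days (Study Schedule, section 6.2). Its distribution is not given, so 3, 7 and 14 days are assumed. Seven days is the mean if lags are uniform over 0 to 14.
- First on-treatment tumour evaluation: end of cycle 2 (section 6.3), with 28-day cycles (section 3.2.2).
- Yardstick medians: phase III apatinib arm, PFS 2.6 months and OS 6.5 months (section 1.1.3.3).
- N = 2000 (section 9.4). The protocol states no target median or precision, so there is no figure of its own to reproduce.

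**Step 1: shift in the median.** In dosed patients, time from consent = L + time from first dose. With a common lag, median from consent = median from first dose + L. One month is taken as 30.44 days, so 3/30.44 = 0.10, 7/30.44 = 0.23 and 14/30.44 = 0.46 months.

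| Assumed lag | Shift (months) | PFS median if 2.6 from first dose | OS median if 6.5 from first dose |
|---|---|---|---|
| 3 days | 0.10 | 2.70 (+3.8%) | 6.60 (+1.5%) |
| 7 days | 0.23 | 2.83 (+8.8%) | 6.73 (+3.5%) |
| 14 days | 0.46 | 3.06 (+17.7%) | 6.96 (+7.1%) |

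**Step 2: scan calendar.** The end of cycle 2 is 2 × 28 = 56 days after first dose. A progression found then is recorded at 56 + L days: 59, 63 or 70 days for the three lags.

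**Step 3: check by simulation.** 400,000 exponential event times were drawn from consent with the yardstick medians, and anyone with an event before dosing was removed. Medians in the patients kept:

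| Lag | PFS from consent / from first dose | OS from consent / from first dose |
|---|---|---|
| Fixed 7 days | 2.84 / 2.61 | 6.73 / 6.50 |
| Uniform 0 to 14 days | 2.83 / 2.60 | 6.74 / 6.51 |
| Fixed 14 days | 3.05 / 2.59 | 6.98 / 6.52 |

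The differences match Step 1. With a spread of lags, the median moves by about the mean lag.

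**Step 4: deaths before dosing.** Under a constant hazard with a 6.5-month median, the share dying within the lag is 1 − 2^(−L/6.5), with L in months. This is 4.8% at 14 days and 2.4% at 7 days.

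**Step 5: comparison with precision.** Assume all 2000 patients are analysed and survival is exponential. The 95% half-width of a median m then lies between 1.96·m/√2000 (every event observed) and 1.96·m/(ln 2·√2000) (distribution-free median, no censoring). For PFS this is 0.11 to 0.16 months, and for OS 0.29 to 0.41 months. A 3-day lag stays below both. A 7-day lag exceeds the PFS half-width but not that of OS. A 14-day lag exceeds both.

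**The case against.** The best counter-argument is that two effects are being mixed. Counting from consent is a declared choice of origin, and a reader can see what the median measures. Only the removal of patients who die before dosing is selection, and such deaths should be few: entry requires an expected survival of at least 3 months and ECOG 0 to 2 (section 4.2.1), and even a constant hazard gives only 2.4% to 4.8%. This stands in part. A consent origin is legitimate when all consented patients are analysed. Here they are not, and the extra length relative to a first-dose clock does not depend on many deaths, because every dosed patient carries the lag.

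Three stronger readings are tempting, and the protocol does not support them.

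- **Both medians are inflated by 0.46 months.** Fourteen days is a ceiling. It reaches the median only if nearly everyone consents at day −14, and most screening tests fall within one week of treatment. The direction is established; the amount is not.
- **The interval is guaranteed event-free for both endpoints.** That is strict for death only. Nothing in section 9.1 removes a patient whose progression is found before dosing and who is then dosed. For progression the guarantee is practical, because no scan is scheduled in the interval.
- **The shift uses up much of the PFS benefit seen in phase III** (2.6 against 1.8 months). That benefit is a difference between randomised arms, whereas this is a shift in the level of a single arm. The protocol plans no comparison with phase III and does not state that trial's time origin. Phase III also left six untreated patients out of its analyses, so its medians may have the same structure.

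**Conclusion.** The point holds as a mismatch between time origin and analysis set, and nothing elsewhere in the protocol corrects it. Relative to a first-dose clock, median OS and median PFS are lengthened by about the typical consent-to-dose lag. That is 0.10 to 0.46 months for assumed lags of 3 to 14 days: roughly 4% to 18% of a 2.6-month PFS and 1.5% to 7% of a 6.5-month OS.

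The size rests on the assumed lag and on phase III medians used only as yardsticks. OS and PFS are secondary and descriptive, and the primary safety analysis is untouched. It is worth correcting because the correction is cheap. With N = 2000, a 7-day lag would already move median PFS by more than its confidence half-width.

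**What to change.** In section 9.2.2 b, define OS and PFS from the date of the first apatinib dose, and state in section 9.3.3 that they are analysed in the FAS.

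If an OS analysis from consent is wanted as a sensitivity analysis, it should include all consented eligible subjects, dosed or not. The same device would not by itself remove the PFS shift: with no scan scheduled before dosing, almost no progression can be recorded in the lag, so adding undosed patients would barely move that median.

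The cost is one phrase in each of two definitions and a named analysis set. The first-dose date is already needed for the exposure summary in section 9.3.2 and for the cycle calendar. No visit, procedure or treatment changes. The downside is slightly shorter reported medians.
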